#### Planned and post hoc examination of potential confounds, mediators and moderator effects

Based upon our primary and secondary analyses above, we expect to observe evidence of variables that confound the causal relationship between the intervention and any associated change in outcome over time. Assuming the presence of multiple influential variables, we will use multivariate path analysis to model theoretically-justifiable pathways. This process is expected to require the specification of mediation and moderation pathways, including sequential and competing pathways. For example, a mediation model will be employed if psychological flexibility, self-compassion and mindfulness scores are associated with baseline and longitudinal QoL scores. If participant age is differentially associated with psychological flexibility, self-compassion, mindfulness and QoL scores, then participant age will be added to the model as a moderator (i.e. moderated-mediation), and so on, as necessary.

#### Covariates (controlling variables)

Where variables are expected to correlate with but not differentially predict outcomes, we will control for the influence of expected covariate variables by including them at the baseline model. The planned covariates consist of sociodemographic and clinical variables, such as age, education level, marital status, type of BC, BC stage, previous chemotherapy treatment, use of psychopharmacological medication, time since diagnosis, recurrence and number of major life events occurring during the previous year.

#### Planned moderation analysis variables

Variables such as awareness of psychological processes, frequency of at-home practice and efficacy expectancy are expected to moderate the efficacy of the intervention upon primary and secondary outcomes. These variables will be included as baseline first-order interactions with the intervention allocation factor and post-intervention outcomes. Interactions will be examined at typical proportions of each factor: the mean and ± 1 standard deviation around the mean. Non-significant interaction effects will be trimmed from the model to preserve model parsimony, though significant main effects will be retained and treated as baseline covariates.

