## Statistical methods

### Statistical methods for primary and secondary outcomes {20a}

#### General analytic procedures

The superiority of the Mind programme over the control group(s) will be tested through the analysis of changes in the primary (cancer-specific QoL) and secondary outcomes (anxiety and depressive symptoms, psychological flexibility, self-compassion, health-related QoL, resources consumption), controlling for sociodemographic and clinical variables and potential moderation effects of variables such as the awareness of psychological processes, the frequency of at-home practice, the number of major life events occurring during the previous year and efficacy expectancy. The Mind programme will be compared against the support group in study 1 and against both the support and treatment as usual (waiting list) groups in study 2. Study 1 also includes immunological and epigenetic markers as secondary outcomes. The analytical approaches for both studies are otherwise comparable.

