#### Analyses by aims

Aim 1: Determine the efficacy of the Mind programme compared to an active (i.e. support group) and/or inactive (i.e. treatment as usual group) control condition at post-intervention and at 6-month follow-up period.

The planned analysis for each outcome is a repeated-measures linear mixed model, including polynomial simple slopes to identify non-linear change over time. Within-group and contemporaneous between-group post hoc comparisons, using independent- or paired-samples *t*-tests (as appropriate), adjusted for multiple comparisons using the modified Bonferroni adjustment, will be performed. The efficacy of the intervention can be inferred through the evaluation of the simple slopes for each treatment condition, whereby the experimental condition demonstrates a significant improvement in QoL scores over time, and this improvement exceeds that of the control condition. The clinical significance of changes presented by each participant will be determined by computing the reliable change index (RCI) and considering mixed models of repeated measures (i.e. growth modelling analysis). In the former, we will calculate primary or secondary outcome RCI for each participant between pre- and post-intervention, as well as pre-intervention and 6 months. An RCI of ± 1.96 is considered statistically significant at *p* = 0.05, and the proportions of participants within each treatment condition who demonstrate significant improvement, decline and no change will be recorded. Fisher’s exact test will be used to examine for significant differences in the proportion of change between treatment allocations. Finally, we will perform correlation analysis between the raw RCI values and demographic variables separately for each treatment condition. This final analysis is used to examine potential predictors of individual change and the nature of that change.

Aim 2: Determine the cost-effectiveness of the Mind programme compared to an active (i.e. support group) and/or inactive (i.e. treatment as usual group) control condition at post-intervention and at 6-month follow-up period.

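### The protocol does not fix whether the superiority model contains moderator interactions, and it keeps or drops those interactions by their p-values, which overstates the ones that stay

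*Protocol article*

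**What the plan says.** Three places in the protocol article's Statistical methods {20a} bear on this.

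- **General analytic procedures** says that superiority is tested "controlling for sociodemographic and clinical variables and potential moderation effects of variables such as the awareness of psychological processes, the frequency of at-home practice", and goes on to life events and efficacy expectancy.
- **Analyses by aims, Aim 1** names no moderator: "The planned analysis for each outcome is a repeated-measures linear mixed model, including polynomial simple slopes to identify non-linear change over time". Efficacy is read from slopes: "The efficacy of the intervention can be inferred through the evaluation of the simple slopes for each treatment condition".
- **Planned moderation analysis variables**, which follows the Aim 3 heading, gives an open list: "Variables such as awareness of psychological processes, frequency of at-home practice and efficacy expectancy are expected to moderate the efficacy". On how they enter: "These variables will be included as baseline first-order interactions with the intervention allocation factor and post-intervention outcomes". On probing: "Interactions will be examined at typical proportions of each factor: the mean and ± 1 standard deviation around the mean". On retention: "Non-significant interaction effects will be trimmed from the model to preserve model parsimony". Significant main effects stay as covariates.

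Two other sections matter. Home practice frequency records at-home practice at the sessions of the Mind programme only. Efficacy expectancy is a yes/no item asked at baseline. No section says that moderators are centred, what level counts as significant, or that a moderator-free model is the primary test.

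**The concern.** Two things are at stake.

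The first is the primary result. While an allocation-by-moderator interaction is in a model, the allocation coefficient is the Mind effect at moderator value zero. If the moderator is centred, that is close to the average effect. If it is not, it is the effect at a raw score of zero or, for expectancy coded 0/1, among women who answered no. If such terms are in the superiority model and the data decide which stay, the quantity tested can differ from one realisation of the trial to the next.

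The second is Aim 3. An interaction that stays only because it was significant is overestimated on average, and a real one that misses significance leaves the model. The Strengths section hopes that subgroup findings will guide treatment customisation, which is the use most exposed to this bias.

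**Working it through.** **Inputs from the Sample size section (study 1).** Up to 150 women, 75 per arm, 1:1; attrition 10–30%; alpha 0.05 (two-sided assumed); power 80%; rho 0.5; detectable SMD 0.51.

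**The plan's own figure.** It reproduces by two routes. The group-by-time F test with N = 150 and no attrition gives f = 0.255, so d = 2f = 0.51. Two means with 60 completers per arm (20% attrition) give (1.960 + 0.842) × √(2/60) = 0.511. I use 120 analysable women below.

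**Assumptions not in the protocol.** Retention at p < 0.05; three independent moderators, two continuous and one yes/no with 80% yes; all measured in both arms and unaffected by treatment; a single post-treatment outcome adjusted for a baseline with correlation 0.5. In the uncentred case, raw continuous scores average 2 SD above zero.

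**Step 1: chance of keeping a null interaction.** 1 − 0.95³ = 0.143. Simulation gives 13–15%.

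**Step 2: what the filter does to a true interaction, moderators centred.**
- Residual SD = √(1 − 0.5²) = 0.866. For a moderator with SD 1 and 1:1 arms, SE = 2 × 0.866/√120 = 0.158.
- With z = effect/SE, P(kept) = Φ(z − 1.96) + Φ(−z − 1.96), and the mean z when kept is z + [φ(1.96 − z) − φ(1.96 + z)]/P(kept).
- Effect 0.25 SD per SD: z = 1.581; P(kept) = 0.353; mean when kept = 1.581 + 0.3705/0.353 = 2.63. Ratio 2.63/1.581 = 1.66.
- Effect 0.15: z = 0.949; P(kept) = 0.158; mean when kept = 0.949 + 0.2335/0.158 = 2.43. Ratio 2.43/0.949 = 2.56.
- Simulation agrees: 0.25 is kept in 33% and overstated 1.72-fold; 0.15 is kept in 15% and overstated 2.58-fold.
- With residual SD 1 (no gain from baseline adjustment), 0.25 is kept in 26% and overstated about 1.9-fold. Averaged over all runs, with nothing filtered, the estimate is 0.247, so the filter is the source of the bias.

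**Step 3: the allocation term after trimming, no true moderation (simulation).**

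| | No interactions | Trimmed, centred | Trimmed, uncentred |
|---|---|---|---|
| Rejection, no Mind effect | about 5% | about 5% | about 12–13% |
| Power at SMD 0.51 | about 87–88% | unchanged | about 82–83% |

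The power loss can be checked by hand. About 14% of uncentred trials keep a term, and power in those was 53% in one run: 0.14 × (0.88 − 0.53) = 0.049, or about 5 points. Other assumed moderators gave 57–70% in those trials and a loss of 2–5 points (0.13 × 0.18 to 0.15 × 0.31).

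**Step 4: at-home practice.** It has no values in the comparator, so its interaction with allocation cannot be estimated. It also arises after randomisation, so it cannot be a baseline term.

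**The case against.** The strongest reply is that the Aim 1 model is given without moderators and that the trimming rule sits under Aim 3, so the superiority test may never contain an interaction. That stands as far as it goes: the text is ambiguous, and a reader who concludes that the primary test certainly carries these terms goes beyond it. But the general statement on superiority says the opposite of a moderator-free test, and nothing settles which governs.

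A second reply is that probing at the mean and ±1 SD suggests centring, and that coding is usually left to an analysis plan. This also has weight: with centring, the allocation term keeps its size and power. Probing points are not a coding rule, however, and ±1 SD does not suit a yes/no item.

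Third, the planned efficacy reading uses slopes and adjusted t-tests, not the single ANCOVA coefficient simulated here. The primary-test figures are therefore indicative.

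Two stronger readings should be resisted. A reader might infer that power collapses to 15–40%. That describes an uncentred interaction kept regardless of its p-value, whereas the trimming rule would remove most such terms. A reader might also infer that trimmed interactions go unreported. The protocol says only that they leave the model.

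**Conclusion.** The point holds in a limited form. The protocol does not fix which model yields the primary Mind effect, and it states a retention rule that biases the interactions it keeps.

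The Aim 3 part does not depend on coding or on how the ambiguity is resolved: about 1.7-fold overstatement at 0.25 SD per SD and about 2.6-fold at 0.15, at 120 analysable women. Those effect sizes and the 0.05 level are assumptions. The direction is not: smaller true interactions are overstated more.

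The primary-test part is conditional. It needs the interactions to be in the superiority model and uncentred; then type I error is about 12–13% and the power loss about 5 points, given the assumed moderator distributions. With centring there is no such effect. The figures are for study 1; study 2 shares the analytical approach but was not simulated.

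This is a free improvement, not a flaw that invalidates the trial.

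**What to change.** - **General analytic procedures and Analyses by aims:** name as the superiority test one model with allocation, visit, allocation-by-visit and a fixed list of baseline covariates, with no moderator interactions. Remove moderation from the sentence on superiority.
- **Planned moderation analysis variables:** delete the trimming sentence. Fit each prespecified baseline moderator, centred, in its own model labelled exploratory. Report every interaction with its 95% CI, significant or not.
- **At-home practice:** take it out of the list of interactions with allocation.

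The cost is wording and slightly longer results tables. No new data are needed and no trial procedure changes.

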### Methods for additional analyses (e.g. subgroup analyses) {20b}

All analyses are described in Sect. 20a, including subgroup analyses.

### Methods in analysis to handle protocol non-adherence and any statistical methods to handle missing data {20c}

All main analysis will be performed as an intention-to-treat (ITT) analysis to provide unbiased estimates of the intervention efficacy regarding the level of participants’ adherence to the study. In such an approach, the participants will be considered according to the group they were originally assigned to regardless of intervention compliance. Missing data will be reported and when MCAR (Missing Completely at Random) or MAR (Missing at Random) occurs, multiple imputation methods will be used to estimate missing values when appropriate. Missing values will be imputed with well-established methods that reduce bias in estimates such as multiple imputation, full information maximum likelihood and empirical Bayes estimation, or multiple imputations with chained equations (MICE), if a substantial amount of missing data exists.

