### Sample size {14}

Regarding study 1, power was considered according to a sensitivity analysis of the likely attainable sample size and compare with the effect sizes estimated by previous meta-analyses and studies suggesting improvements in mood and QoL between SMD = 0.2 to 0.6, favouring psychotherapies over controls [15, 16]. It is anticipated that up to *N* = 150 (*n* = 75 per group) participants will be recruited, and attrition rates of between 10 and 30% can be expected. The planned analysis specifies a repeated-measures linear mixed models analysis, a group allocation of 1:1, alpha of 0.05, a minimum of 80% power, three assessment points and a compound symmetry correlation matrix (rho = 0.5; Lu et al., 2008). Under these parameters, the study is powered to reliably detect a between-group difference on cancer-specific QoL at follow-up of SMD = 0.51 (WebPower; [37]).

For study 2, the GLIMMPSE software was used to calculate the minimum sample size required for a three-armed linear mixed model with three measurements. Assuming a comparable effect size to that estimated in study 1 (SMD = 0.5) favouring the Mind intervention group over waiting list at 6 months for QoL, an unstructured correlation matrix, a group allocation of 2:2:1, alpha of 0.05 and a minimum of 80% power, the minimum sample size required is *N* = 117. To account for up to 30% attrition, this sets the minimum total sample size at *N* = 153 [38].

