### Limitations

There are several potential limitations to consider. First, the high risk of participant dropout. Patients may not be available or willing to complete post-treatment or follow-up assessments, despite research team efforts to retain study participation (e.g. regular contact, reminders, gifts). Second, recruiting patients already overwhelmed with BC treatment agenda is challenging. Finally, it is possible that our findings may not be generalised to some groups of women with BC (e.g. patients from remote rural areas or digital naïve patients).

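### The imputation rule rests on conditions that cannot be checked or are not defined, so the t-tests, reliable-change proportions and Fisher's test may silently become responder-only analyses

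*Protocol article*

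**What the plan says.** Section {20c} gives two sentences on imputation. The first makes it depend on the missingness mechanism: "Missing data will be reported and when MCAR (Missing Completely at Random) or MAR (Missing at Random) occurs, multiple imputation methods will be used", further qualified as applying where appropriate. The second makes it depend on quantity. It lists "multiple imputation, full information maximum likelihood and empirical Bayes estimation, or multiple imputations with chained equations (MICE), if a substantial amount of missing data exists", with no threshold and no statement of which method serves which analysis.

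The analyses are in {20a}, Analyses by aims, Aim 1. The main one is unconditional: "The planned analysis for each outcome is a repeated-measures linear mixed model, including polynomial simple slopes to identify non-linear change over time". It is followed by "Within-group and contemporaneous between-group post hoc comparisons, using independent- or paired-samples" t-tests with a multiplicity adjustment, individual RCIs from baseline to post-treatment and to 6 months, and Fisher's exact test on the proportions improving, declining or unchanged.

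On expected loss, Sample size {14} says for study 1 that "attrition rates of between 10 and 30% can be expected", and study 2 allows for up to 30%. The first item under Limitations is "First, the high risk of participant dropout. Patients may not be available or willing to complete post-treatment or follow-up assessments". Section {18b} continues outcome collection for all participants. The sensitivity analysis it names concerns sessions attended, not missing outcomes.

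**The concern.** A missing-data rule should be one that two analysts would apply in the same way before seeing results. This one is not. Data can give evidence against MCAR, but MAR and MNAR can fit the observed data equally well, so the mechanism trigger rests on opinion. The quantity trigger has no threshold. The two can also disagree: MAR may be thought plausible with little missing, or much may be missing while MAR is doubted. The text does not say which then governs.

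What is at stake is the set of analyses that need an observed follow-up score. If imputation is not triggered, the between-arm and paired t-tests, the RCI proportions and Fisher's test leave out every woman who did not return that survey. They would then address a different population from the mixed model reported beside them, and the choice could be made after the data are in hand.

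**Working it through.** **1. The plan's own figure.** Section {14} gives a detectable SMD of 0.51 for study 1 (75 per arm, alpha 0.05, 80% power, three assessments, compound symmetry with rho = 0.5). Taking alpha as two-sided, SMD = (1.960 + 0.842) × √(2/n).
- n = 75: 2.802 × √(2/75) = 0.457
- n = 60 (20% attrition): 2.802 × √(2/60) = 0.511
- n = 52.5 (30% attrition): 0.547

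A repeated-measures noncentral-F calculation at N = 150 gives f = 0.255, so 2f = 0.509. The 0.51 is therefore reproduced, either as 20% attrition or as the full 150; the text does not say which. It is used below as the assumed true effect at post-treatment and at 6 months.

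**2. Set-up.** Large-sample simulation, three visits, SD 1, rho = 0.5. The 6-month score goes missing with a probability that is logistic in the outcome, worse scores being lost more often. The slope is an assumption: the protocol gives none, so 1 and 1.5 log-odds per SD are shown. Two estimates are compared:
- responders: the simple 6-month mean difference, as in an unimputed t-test;
- likelihood: an estimate using all observed visits, as the mixed model does when its means are free by arm and visit.

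**3. Dropout in Mind follows the observed post-treatment score; control dropout is random at the same rate (MAR).**

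| Slope | Attrition | Responders | Change from 0.51 |
|---|---|---|---|
| 1 | 10% | 0.550 | +8% |
| 1 | 20% | 0.598 | +17% |
| 1 | 30% | 0.644 | +26% |
| 1.5 | 10% | 0.570 | +12% |
| 1.5 | 30% | 0.671 | +32% |

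Likelihood (slope 1.5) gives 0.510 and 0.506; imputation from baseline and post-treatment scores (slope 1) gives 0.505–0.514. A rerun agreed with the responder figures to within 0.01. They also make sense algebraically: responder bias = rho × (mean post-treatment score of Mind responders minus that of all Mind women). The largest entry implies (0.671 − 0.51)/0.5 = 0.32 SD of selection at post-treatment.

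**4. Other dropout patterns on the observed score (slope 1.5).** With the same form and 30% in both arms, responders give 0.515 and likelihood 0.516. With the same form but 30% in control and 10% in Mind, responders give 0.404 against a true 0.507, so the bias runs against Mind; likelihood gives 0.507.

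**5. Dropout on the unseen 6-month score (MNAR, slope 1.5).** Here the likelihood estimate moves too. It is 0.593 at 10% and 0.744 at 30% with selection in Mind only, 0.514 when both arms lose 30% alike, and 0.357 when control loses 30% and Mind 10%. A simple shift shows the scale. If lost Mind women are worse by delta than MAR predicts, the effect is 0.51 − (dropout × delta). At 30% dropout and delta = 0.5 this is 0.51 − 0.15 = 0.36. The shift that removes the effect altogether is 0.51/0.30 = 1.7 SD at 30% and 0.51/0.10 = 5.1 SD at 10%.

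**The case against.** The strongest reply is that the primary result is safe. That stands: {20a} specifies the mixed model without condition and infers efficacy from its slopes. The model uses partial data and needs no imputation under MAR. A reader might infer that the trial's main estimate turns into an estimate for retained women, but the documents do not support that; the description fits only the unimputed comparisons.

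Three other strong readings also fail.
- A reader might say the plan wrongly promises freedom from missing-data bias. The sentence reads "intention-to-treat (ITT) analysis to provide unbiased estimates of the intervention efficacy regarding the level of participants’ adherence to the study", so it ties the claim to adherence, which ITT does address. It need not be deleted.
- A reader might say outcome-related dropout is not handled. Dropout related to observed outcomes is handled by the mixed model and by the listed methods; only dropout related to unseen outcomes is not.
- A reader might count the lack of an MNAR analysis as an error. That detail is commonly left to an analysis plan or full protocol not shown here, so its absence alone is no finding.

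It is also fair that one-sided dropout is assumed rather than documented. The support group has the same length, format and non-completer rule as Mind, and reminders and the voucher apply to everyone. Hence the balanced and reversed cases above. What the reply does not answer is that the rule, as stated, cannot be applied consistently.

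**Conclusion.** The point holds in a limited form. Section {20c} fixes two different imputation triggers, one unverifiable and one undefined. Under MAR this leaves the primary mixed model untouched, but it leaves open whether the t-tests, RCI proportions and Fisher's test cover all randomised women or responders only.

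For the 6-month between-arm difference, the gap is about 0.55–0.67 against 0.51 (+8% to +32%) at 10–30% attrition. That rests on an assumed log-odds slope of 1 to 1.5 per SD on the observed post-treatment score, acting in Mind only. It is near zero with like dropout in both arms, and negative (0.404) when control loses 30% and Mind 10%. The size for the RCI proportions was not computed. The wording should be corrected before outcome data are examined; the defect does not by itself undermine the primary conclusion.

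**What to change.** Amend {20c} and the matching text in {20a}:

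1. Delete the mechanism and quantity conditions. State MAR as the primary assumption, without a test and without a threshold.
2. Fit the mixed model to all randomised women. Take the between-arm and within-arm contrasts at each visit from that model instead of separate t-tests; the planned multiplicity adjustment can be kept.
3. For the RCI, Fisher and QALY analyses, specify one multiple imputation model, run by arm, with baseline and post-treatment scores and chemotherapy status as predictors. Add sessions attended in the intervention arms only, since the study 2 waiting list has none.
4. Add a delta-shift (tipping-point) analysis of the 6-month primary contrast, allowing different shifts by arm and run against each control in study 2. Present it as supporting evidence, not as a success criterion.

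The cost is revised wording and slightly more analysis with methods already named; no new data are needed. The sensitivity estimates may be less favourable to Mind.
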